### Statistical analysis plan

The analysis will include all participants enrolled in the study. Summary statistics will consist of counts and percentages for categorical variables, mean and standard deviation for continuous variables, or median and quartiles (25th and 75th percentiles) for non-symmetrical continuous variables.

The primary outcome, DAH_30_, will be modelled using median or, more generally, quantile regression (Koenker & Bassett, 1978). As DAH_30_ is left skewed with a spike at zero, it is more relevant to model the median that is closer to the major distribution mode and directly interpretable (Koenker & Bassett, 1978). Difference in median DAH_30_ between the two groups (patients with iron deficiency versus those who are iron replete) will be obtained unadjusted (including recruiting hospital) and adjusted for potential known confounders, namely EuroSCORE-II and body surface area (in addition to recruiting hospital). A similar strategy will be used for DAH_90_. In addition, a propensity score analysis will be carried out. Using logistic regression, the probability (propensity score) that a participant would have been allocated to the iron-deficient or iron-replete group will be estimated by including in the model potential confounding baseline characteristics (EuroSCORE-II, diet and CRP). This propensity score will be used as a covariate in adjusting the quantile regression model with the group variable and hospital. Balance and underlying assumptions (i.e. linearity and no interaction between the group and propensity score) will be checked.

Additional secondary binary outcomes will be analysed using logistic regression and continuous outcomes using linear regression adjusted for the baseline reading where applicable. A repeated measures analysis based on mixed linear models will also be conducted for blood haemoglobin. Time-to-event will be analysed using Cox proportional hazards regression. Safety endpoints and postoperative complications that exhibit small numbers will be analysed using exact logistic regression. All statistical analyses will be conducted both unadjusted (including hospital) and adjusted for potential known confounders (in addition to hospital).

Subgroup analyses will be performed to explore heterogeneity in the effect between centres, sex, age groups and estimated glomerular filtration rate grouping by including a term for subgroup and interaction between subgroup and group in the models. An exploratory analysis will be performed stratifying participants by sex and haemoglobin strata (130–139 g/L and ≥ 140 g/L for men, and 120–129 g/L, 130–139 g/L and ≥ 140 g/L for women). Finally, additional analyses will be performed based on different definitions of iron deficiency used in the literature previously (TSAT < 20% vs. TSAT ≥ 20% and serum ferritin < 100 μg/L vs. ≥ 100 μg/L) (Richards et al., 2020). The outcomes analysed will be DAH_30_, DAH_90_, readmission up to postoperative day 90 and postoperative complications (including infection). Analyses will use complete cases. If the proportion of missing data is above 5% (Jakobsen et al., 2017), additional analysis using inverse probability weighting will be used where complete cases will be weighted by the inverse of their probability of being a complete case (SR S, IR W., 2013).

All statistical tests will be performed, and confidence intervals reported at the two-sided 5% level of significance. To control the overall Type I error rate across DAH_30_ and DAH_90_, a hierarchical testing strategy is planned where the null hypothesis of no difference in median DAH_90_ will be tested at the two-sided 5% significance level only if the null hypothesis of no difference in median DAH_30_ is rejected at the two-sided 5% significance level. All analyses will be carried out in Stata 16.1 (Stata Corporation, College Station, TX, USA).

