## Abstract

**Background:**

Pre-operative anaemia has been associated independently with worse outcomes after cardiac surgery in adults and is often caused by absolute or functional iron deficiency. Iron deficiency is a continuum ending with anaemia, and therefore it is plausible that pre-operative early or ‘non-anaemic’ iron deficiency may also be associated with worse outcomes in patients undergoing cardiac surgery.

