### Sample size and justification

Data assumptions for the primary outcome were obtained from a retrospective review of similar cases at one of the participating hospitals (Miles et al., 2018b). Whilst DAH_30_ was not explicitly reported as part of this dataset, it was obtained on re-analysis. The primary endpoint (DAH) has a left-skewed distribution with a spike at 0, mainly due to deaths in hospital post-surgery. Power was obtained by simulations (20,000). DAH-looking data were generated by simulating first length of stay using a lognormal distribution, truncating it at 28 days (a plausible maximum based on existing data) and finally computing DAH as length of stay (days) subtracted from 28. Such data are bimodal with a spike at 0 as required. The lognormal distribution was calibrated to generate DAH with a median of 23 days and 5% zeroes in the NAID group. A sample size of *n* = 480 (240/group) participants has 83% power to detect a median increase of 1.25 days using the Wilcoxon sum rank test for the analysis and allowing for up to 5% dropout in each group. Sample size calculations were performed in R 3.4.0 (R Foundation for Statistical Computing, Vienna, Austria).

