## Current status of the trial

The first patient was recruited on 26 March 2018. Enrolment was completed in the iron-deficient group (*n* = 240) on 6 January 2021, and in the iron-replete group (*n* = 240) on 11 February 2021. Participant follow-up concluded in May 2021. Aggregate characteristic data from the 480 participants enrolled in the study are shown in Table 2.

**Table 2 Tab2:** Aggregate pre-operative characteristics of the study cohort

Characteristics	Value (***n*** = 480)
Female	95 (19.7%)
Age (years)	64.1 (11.6)
Height (m)	1.72 (0.09)
Weight (kg)	88.4 (17.0)
BMI (kg/m^2^)	29.7 (5.1)
BSA (m^2^)	2.04 (0.23)
Previous MI	72 (15%)
Congestive cardiac failure	112 (23.3%)
Peripheral vascular disease	24 (5%)
COPD	49 (10.2%)
Diabetes mellitus	118 (24.5%)
Chronic renal impairment	44 (9.2%)
Active smoker	75 (15.6%)
EuroSCORE-II (%)	1.08 (0.69–1.74)
LVEF > 50%	417 (86.9%)
LVEF 41–50%	54 (11.3%)
LVEF 31–40%	6 (1.2%)
LVEF ≤ 30%	3 (0.6%)
Pre-operative PASP ≥ 31 mmHg	45 (9.3%)

*BMI* body mass index, *BSA* body surface area, *MI* myocardial infarction, *COPD* chronic obstructive pulmonary disease, *EuroSCORE* European System for Cardiac Operative Risk Evaluation, *LVEF* left ventricular ejection fraction, *PASP* pulmonary artery systolic pressure

The postoperative day 45 haemoglobin will not be reported in the primary manuscript at this stage, and instead will be the subject of an additional hypothesis-generating analysis examining specific secondary outcomes (DAH_90_ and readmission). At the time of writing, formal database lock and analysis has not yet been performed.

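### Effect modification by haemoglobin, age and eGFR is planned only in categories; adding continuous interaction terms beside them would cost wording only

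*Protocol article*

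**What the plan says.** The Statistical analysis plan of the protocol article treats effect modification in two ways.

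- Subgroup analyses examine "heterogeneity in the effect between centres, sex, age groups and estimated glomerular filtration rate grouping by including a term for subgroup" and a subgroup-by-iron-group interaction. The number of age and eGFR groups and their cut-points are not given.
- Separately, "An exploratory analysis will be performed stratifying participants by sex and haemoglobin strata". The strata are 130-139 and 140 g/L or more for men, and 120-129, 130-139 and 140 g/L or more for women. No interaction test is stated for these strata.

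No continuous version of any of the three modifiers is described. Table 2 (Current status of the trial) reports 95 women among 480 participants, hence 385 men. That section also says that database lock and analysis had not yet taken place.

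**The concern.** Haemoglobin and age are recorded as numbers, and eGFR is calculated from an equation (Assessments). The abstract's premise is that "Iron deficiency is a continuum ending with anaemia", so a natural secondary question is whether the NAID effect changes gradually as haemoglobin nears the anaemia threshold, with age, or with renal function. Grouping discards the variation within each group and, with more than two groups, spends extra degrees of freedom. All men at 140 g/L or above fall into one open stratum, so a gradient among them cannot be seen.

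Two misreadings are at stake. A real gradient may be missed and reported as consistency. Conversely, very imprecise estimates in the women's strata may be compared by eye and taken as heterogeneity.

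**Working it through.** **1. The plan's own power.** Sample size and justification states that "The lognormal distribution was calibrated to generate DAH with a median of 23 days and 5% zeroes in the NAID group", with stay capped at 28 days and days at home equal to 28 minus stay. Median stay is therefore 28 - 23 = 5 days, and the SD of log stay is ln(28/5)/1.645 = 1.047. With a replete median of 24.25 (stay 3.75 days), 20,000 simulated trials and a two-sided 5% Wilcoxon test, power is 81.5% at 228 per group (240 less 5%) and 83.3% at 240. The article says "participants has 83% power to detect a median increase of 1.25 days using the Wilcoxon sum rank test for the analysis". The outcome model reproduces that figure within 2 points.

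**2. Age and eGFR.** The documents give no power for any heterogeneity test, so a benchmark is assumed: a linear gradient that a continuous 1-df interaction test detects with 80% power at two-sided 5%. This needs a non-centrality of 7.85. Grouping a normally distributed modifier multiplies the non-centrality by the share of variance retained.

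| Modifier entered as | Share retained | df | Non-centrality | Power | Power at half the gradient (non-centrality / 4) |
|---|---|---|---|---|---|
| Continuous | 1 | 1 | 7.85 | 80% | 29% |
| Median split | 2/π = 0.637 | 1 | 5.00 | 61% | 20% |
| Tertiles | 0.793 | 2 | 6.22 | 60% | 18% |

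**3. Haemoglobin, if the five strata were compared formally (4 df).** The article gives no haemoglobin distribution. Assumed: men mean 142-150, SD 10-12 g/L, truncated at 130; women mean 130-138, SD 9-11 g/L, truncated at 120; iron status independent of sex and haemoglobin. Expected stratum sizes are then 59-133 and 252-326 for men, and 15-42 in each stratum for women. The benchmark is again 80%.

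- Effect linear in absolute haemoglobin: share retained 0.56-0.71, power 35-44%.
- Effect linear in distance above the sex-specific lower limit (130 or 120 g/L): share retained 0.46-0.62, power 29-38%.
- Effect present only in each sex's lowest stratum: strata 60%. A linear term gives 37-49% on the absolute scale and 42-57% on the distance scale.
- Step at 140 g/L: strata 60%. A linear term in absolute haemoglobin gives 52-61%.

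**4. Women's strata.** 95/3 is about 32 per stratum, or about 16 per iron group if evenly split. Under the step 1 outcome model:

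| Women per iron group | SD of difference in medians (days) | 95% half-width (days) | Power for 1.25 days |
|---|---|---|---|
| 10 v 10 | 2.77 | 5.4 | 8% |
| 16 v 16 | 2.12 | 1.96 × 2.12 = 4.2 | 9-11% |
| 20 v 20 | 1.90 | 3.7 | 10-13% |
| 48 v 47 (all women) | 1.21 | 2.4 | 17-25% |

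At 16 v 16 the estimate has the wrong sign in about 26% of runs.

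**5. A simulation not relied on.** Median regression with kernel standard errors was also simulated (1,000 trials per scenario, gradient 1.25 days per SD). It gave 74% power continuous, 53% with a median split and 55% with tertiles; for haemoglobin, 74% continuous and 51% with five strata. With no gradient, however, these tests rejected in 8.6%, 8.7%, 11.7%, 7.5% and 16.0% of runs respectively, so the powers are not comparable at the 5% level. The result does show that the choice of standard error matters for such tests.

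**The case against.** The strongest reply is that these are secondary and exploratory analyses, that details of the age and eGFR groups belong in an analysis plan not shown here, and that categories are easy to report. Several parts of this stand.

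- A reader might infer that the plan loses about 20 points of power in its heterogeneity tests. The documents do not support that as a property of the plan. For haemoglobin no test is stated, and for age and eGFR the number of groups is unknown. The figure holds only for a median split or tertiles under a steep linear gradient. A gradient of 1.25 days per SD around a mean effect of 1.25 days already means 2.5 days at one SD below the mean and none at one SD above. At half the benchmark gradient the loss is about 9-11 points, and every version of the test is weak.
- A reader might also infer that continuous modelling should replace the categories. If the effect sits only just above the anaemia threshold, the strata do better than a linear term. The shared bands also let men and women be compared at the same absolute haemoglobin, and the lowest limits follow from excluding anaemia by the cited WHO criteria.
- The abstract's continuum concerns iron deficiency progressing to anaemia. It does not say that the NAID effect changes linearly with haemoglobin.
- Imprecision in women comes mainly from there being only 95. Even undivided they give a half-width of about 2.4 days. A pooled continuous model gains precision partly by assuming one slope for both sexes.

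What does not fall is that categories are the only form described for all three modifiers, and that a continuous term beside them gives a view of a gradual change which the plan otherwise lacks.

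**Conclusion.** The point holds as a low-cost improvement to secondary and exploratory analyses, not as an error that threatens the study. For age and eGFR, grouping costs about 20 points of interaction power under a linear gradient detectable with 80% power, and less in absolute terms under a weaker one. For haemoglobin, any loss is conditional on a formal comparison that the article does not state. It would be large under a linear gradient (80% to about 29-44%), and absent or reversed under most threshold effects. These figures rest on the assumed benchmark and haemoglobin distributions.

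The finding on women is firmer because it uses the plan's own outcome model and the enrolled count. A half-width of about 4.2 days against 1.25 days means that stratum estimates in women cannot be read as evidence for or against heterogeneity. Only the even split into cells of 16 is assumed, and cells of 10 to 20 lead to the same conclusion. The primary comparison of DAH30 is unaffected.

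**What to change.** Keep the planned categories and add to the Statistical analysis plan:

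- For each of haemoglobin, age and eGFR, fit one model on all participants with iron group, the continuous modifier and their product, including sex in the haemoglobin model.
- Use bootstrap standard errors, and check linearity with a restricted cubic spline.
- Report the estimated NAID difference with its confidence interval at a few values of each modifier chosen in advance.
- Present the five haemoglobin strata as descriptive, with counts per iron group, and state that the women's strata are too small to support conclusions about heterogeneity.
- Label all of this exploratory.

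The cost is wording and a little analysis time. The data are already collected, and analysis had not begun when the article was written. The downsides are a few extra exploratory tests, and a linear term that assumes a roughly linear gradient shared by men and women. The spline check and the retained categories limit the reliance on linearity, but the spline spends degrees of freedom of its own.

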## Background

Anaemia has been independently associated with worse outcomes after cardiac surgery (Rössler et al., 2020; Klein et al., 2016; Hogan et al., 2015; Miles et al., 2018a). Outside the surgical context, anaemia has been associated with reduced exercise capacity, higher incidence of infection and reduced quality of life (Lopez et al., 2016). In the adult patient undergoing cardiac surgery, pre-operative anaemia is independently associated with increased mortality, increased hospital stay, and increased allogeneic transfusion requirement (Klein et al., 2016). Whilst there are multiple possible causes of reduced pre-operative haemoglobin concentration in this cohort, iron deficiency is most frequently implicated (Hung et al., 2015; Muñoz et al., 2017a; Karski et al., 1999; David et al., 2013). The relationship between iron deficiency and anaemia represents a continuum, with iron deficiency anaemia representing advanced iron deficiency (Miles & Story, 2019). In a recently reported observational study using data previously collected for another prospective randomised trial (Spahn et al., 2019), Rössler et al. articulated this graduated association. In this study, patients who were not iron deficient or anaemic had a mortality of 2%, increasing to 4% in patients with anaemia unrelated to iron deficiency, 5% in patients with non-anaemic iron deficiency (NAID) and 15% in patients with iron deficiency anaemia. The physiology of iron handling provides biological plausibility for this observation—whilst 60% of iron stores are involved in erythropoiesis, a further 30% is integral to respiratory chain function, and 10% is incorporated into myoglobin (Suominen & Punnonen, 1998). By the time iron deficiency is sufficiently advanced to cause anaemia, non-erythroid compartments have already been depleted. It is therefore possible that iron deficiency, in the absence of anaemia, might be associated with worse postoperative outcomes, although not to the same degree as iron deficiency anaemia.

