### Outcomes

The primary outcome will be DAH_30_. A secondary outcome measure of special importance will be DAH_90_. Additional secondary outcomes measures will be duration of acute hospital stay, duration of intensive care admission during initial hospital stay, requirement for readmission to acute care within the first 90 days postoperatively, requirement for allogeneic blood transfusion, and haemoglobin concentration relative to baseline measured on postoperative day 3, acute care discharge (or closest approximate value), and at one of the two participating centres on postoperative day 45.

Health-related quality of life outcomes to be assessed are functional status at baseline and postoperative day 30 as measured by the 5-level European Quality of Life Score (EQ-5D-5L) questionnaire (Herdman et al., 2011), disability status at baseline and postoperative day 90 as measured by the World Health Organization Disability Assessment Schedule (WHODAS 2.0) questionnaire (Shulman et al., 2015), and recovery from surgery on postoperative day 3 as measured by the 15-item Quality of Recovery (QoR-15) questionnaire (Stark et al., 2013).

As the study does not involve an intervention, safety and efficacy related outcomes will not be measured per se. However, postoperative complications (including death) have been defined a priori by system using clinical and laboratory criteria and will be reported as part of the study, effectively serving as a safety endpoint (Appendix 1).

All study results will be reported in keeping with the Strengthening the Reporting of Observational Studies in Epidemiology (STROBE) guidelines (von Elm et al., 2007).

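### The complete-case rule and its weighted backup treat death as missing data for WHODAS 2.0 and EQ-5D-5L, so these comparisons are among survivors only and can understate a disadvantage in the iron-deficient group

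*Protocol article*

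**What the plan says.** The section Statistical analysis plan opens with "The analysis will include all participants enrolled in the study". It analyses "continuous outcomes using linear regression adjusted for the baseline reading where applicable", which covers the three questionnaire scores. Its missing-data rule is "Analyses will use complete cases". Above a 5% threshold it adds a second step: "additional analysis using inverse probability weighting will be used where complete cases will be weighted by the inverse of their probability" of being complete.

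The Outcomes section and Table 1 place QoR-15 at day 3, EQ-5D-5L at baseline and day 30, and WHODAS 2.0 at baseline and day 90. The wording for the last is "disability status at baseline and postoperative day 90 as measured by the World Health Organization Disability Assessment Schedule (WHODAS 2.0) questionnaire". The article gives no value, rank or target population for these scores in patients who have died.

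Death is treated differently in days alive and at home (DAH). The Background describes DAH as a composite that includes mortality, and Sample size and justification says: "The primary endpoint (DAH) has a left-skewed distribution with a spike at 0, mainly due to deaths in hospital post-surgery".

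**The concern.** A patient who dies before the visit cannot have a score, so a complete-case linear regression removes that patient. The weighted analysis then gives more weight to survivors who resemble the dead at baseline, as though the dead had lived and answered. There is no unobserved day-90 WHODAS score to recover for someone who died before day 90.

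This matters if the groups lose patients to death at different rates, and the article gives reason to expect that. Its hypothesis is worse outcome in NAID. Its Background cites an observational study with mortality of 2% in patients neither anaemic nor iron deficient and "5% in patients with non-anaemic iron deficiency (NAID) and 15% in patients with iron deficiency anaemia". DAH keeps in-hospital deaths at the bottom of its scale, while the questionnaires drop them. The questionnaire results could therefore look milder than DAH30 or DAH90 partly because of who was left to answer.

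**Working it through.** The article states no power or detectable difference for the questionnaires, so there is no figure of its own to reproduce on this point. Its 83% power for DAH30 does reproduce by simulation (81.5% at 228 per group, 83.4% at 240) but does not bear on this question.

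**Inputs**
- Mortality of 5% (NAID) and 2% (replete): Background, from a cited study; its follow-up time is not given.
- 240 per group, up to 5% dropout: Sample size and justification, so 240 × 0.95 = 228.
- Median EuroSCORE-II of 1.08%: Table 2.
- Assumed, not in the article: WHODAS on a 0–100 scale with higher worse, survivor mean m of 10 to 20 in both groups, survivor SD 15, death scored 100.

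**1. Does the weighted analysis run?** Deaths would be 240 × 0.05 = 12 and 240 × 0.02 = 4.8. Pooled, that is 16.8/480 = 3.5%, so deaths alone do not pass the 5% threshold. Other missing data might take the total past it.

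**2. Difference in means.** Among survivors it is m − m = 0. With death scored 100 it is (0.05 − 0.02) × (100 − m):
- m = 10: 2.70
- m = 15: 2.55
- m = 20: 2.40

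**3. Detectable difference on the same scale (80% power, two-sided 5%, m = 15).** Scoring deaths at 100 widens the SD:
- NAID variance: 0.95 × 225 + 0.05 × 0.95 × 85² = 556.9, SD 23.6.
- Replete variance: 0.98 × 225 + 0.02 × 0.98 × 85² = 362.1, SD 19.0.
- Detectable: 2.8 × √((556.9 + 362.1)/228) = 5.6 points.
- Ratio: 2.55/5.6 = about 45%.

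**4. The same on a rank test.** With equal survivors, the probability that a NAID patient does worse is 0.5 + (0.05 − 0.02)/2 = 0.515. The detectable shift from 0.5 is about 2.8 × √(2/(12 × 228)) = 0.076. Ratio: 0.015/0.076 = about one-fifth.

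**5. Lower mortality.** Assume pooled mortality of 1.08% and the same 2.5:1 ratio. Replete is 2 × 1.08/3.5 = 0.62%, NAID 1.54%, difference 0.93 percentage points.
- Means: 0.0093 × (100 − m) = 0.7 to 0.8 points.
- Detectable at m = 15, by the formula in step 3: variances 331.3 and 267.9, so 2.8 × √(599.2/228) = 4.5 points. Ratio: 0.79/4.5 = about 17%.
- Rank test: 0.0046/0.076 = about 6%.

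**6. Equal mortality.** At 5% in both groups the difference is 0 with or without deaths scored.

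**7. Attenuation shown another way.** Suppose the patients lost are exactly the worst scorers of a normal distribution, 5% versus 2%. The complete-case difference then moves by 0.06 SD in favour of the group with more losses: a true disadvantage of 0.20 SD shows as 0.14, and 0.10 as 0.04. Over assumed losses from 3% versus 1% to 10% versus 5%, the move is 0.04 to 0.09 SD.

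**The case against.** **This is a condensed article, and the handling of death may be set out in a full protocol or analysis plan.** That is possible. But the complete-case rule and its weighting backup are stated here, and applied as written they drop the dead. They also sit badly with the opening statement that all enrolled participants will be analysed.

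**The scope of the rule is ambiguous.** The complete-case sentence follows a list of outcomes for the alternative iron-deficiency definitions, and the questionnaires are not on that list. This stands as a point of wording. A general reading is the natural one, because the article has no other missing-data rule.

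**A survivors-only contrast is legitimate.** This stands. If survivors are equal, 0 is the correct answer for survivors. The gap is that the article does not say this is what is being estimated, and weighting to represent the dead does not fit that target.

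**The mortality input is poorly matched.** This largely stands. The cited study defined iron deficiency by ferritin alone, while this is an elective cohort with a low median EuroSCORE-II. Hence the range in the working.

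**Death is captured elsewhere.** This is true: it enters DAH30 and DAH90 and is reported among complications. The Background also rests its question about worsened recovery on laboratory measures and transfusion as well as these scores. This limits the consequence to secondary outcomes.

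A reader might infer that the group with more deaths will look healthier than the other. The documents do not support that. With equal survivors the observed difference is 0, and with a true disadvantage of 0.10 or 0.20 SD it shrinks but keeps its sign. A reversal (0 showing as −0.06 SD) needs no true difference and losses confined to the worst scorers.

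**Conclusion.** The point holds as one of attenuation in secondary outcomes. As written, WHODAS 2.0 and EQ-5D-5L are compared among survivors without saying so, and the weighted backup lets survivors represent the dead. If NAID carries more deaths, a true disadvantage is understated; if death rates are equal, it is not.

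For WHODAS the amount is 2.4 to 2.7 points at 5% versus 2% mortality and 0.7 to 0.8 points at mortality near 1.08%. This rests on the assumed survivor mean, SD and death score, and on the assumed 2.5:1 ratio in the low-mortality case. No EQ-5D-5L figure is given because the article states no scoring for it.

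A reader might also divide 2.55 by a detectable difference of 2.8 × 15 × √(2/228) = 3.93 and conclude that about two-thirds of a detectable effect is hidden. That sets a death-inclusive difference against a survivors-only SD. On a consistent scale the share is about 45% for means and one-fifth for ranks, falling to about 17% and 6% at the lower mortality.

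QoR-15 is a separate matter. Few deaths are likely by day 3, so the loss there would mainly be patients too ill to answer, and weighting may partly help if it includes predictors of illness. The primary outcome is not affected.

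**What to change.** Before database lock, which the article says had not yet happened:

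- State that the complete-case and weighted analyses of WHODAS 2.0 and EQ-5D-5L estimate a difference among survivors.
- Exclude deaths from the weighting model, so that weights apply only to patients alive at the visit.
- Add a sensitivity analysis, whether or not the 5% threshold is passed, that ranks death as worse than every observed score and compares groups by a rank-based or quantile method. Show it beside the survivors-only result.
- Report by group the numbers who died and the numbers alive without a score.
- For QoR-15, report non-responders by group. Use a worst-rank sensitivity analysis only if the reason for non-response was recorded; Table 1 lists no such item, and follow-up has ended.

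The cost is a few sentences of analysis wording and one extra analysis per score, since Table 1 already collects mortality at days 30 and 90. The drawback is that a death-inclusive score mixes death with quality of life, which is why both results should be shown.
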